**Figure 2 F2:**
[figure not shown]
Follow-up over the first 6 months (M) for patients treated with surgery alone in the EGeSOR study.

During follow-up, the patient has access to the resources provided by the local geriatric network: geriatric rehabilitation unit, geriatric day hospital, geriatric and/or oncology community centre, geriatric nursing home intervention, and home nursing care.

### Intervention geriatrician

The intervention geriatricians involved in the study are senior geriatricians with a mean of 3 years of post-degree experience in geriatrics. Before inclusion of the first patient in their centre, the EGeSOR coordination team composed of four geriatricians [[name]] provided the intervention geriatricians with a half day of training in the EGeSOR intervention and in the specific features of HNSCC.

### Endpoints

Table 
2 shows the primary and secondary endpoints. The primary endpoint is a composite criterion evaluated 6 months after randomisation and including death, an at least 2-point decrease in the Activities of Daily Living [ADL] score
[27] versus baseline, and at least 10% weight loss versus baseline. A clinical research assistant blinded to the randomisation arm uses a standardised measurement guide to adjudicate the ADL score and weight. Weight is measured to the nearest 0.1 Kg using an electronic scale [Seca Model 876, Birmingham, United Kingdom]. Our decision to include functional and nutritional measures into the primary endpoint rests both on sound evidence that these measures influence treatment feasibility, patient survival, and quality of life; and on the potential for appropriate management to reverse functional impairments and weight loss.

### Random assignment

After including each patient and obtaining the panendoscopy and computed tomography or magnetic resonance imaging findings to allow TN staging, the ENT physician or clinical research assistant records the centre, patient age, tumour site, and TN stage into an online central randomisation system [RandoWeb, Paris, France]
[28]. The software automatically checks the data for completeness and consistency then allocates the patient to the intervention group or control group. All patients receive standard HNSCC therapy. The randomisation system applies a minimisation programme to balance the two groups regarding centre, age [<or ≥80 years], T stage [<or ≥ T2], N stage [<or ≥ N2], and tumour site [oral, oropharyngeal, hypopharyngeal, or laryngeal]. Minimisation randomly allocates the first patient to a group then allocates each subsequent patient to the group that produces the smallest difference between treatment groups regarding the five above-listed factors
[29]. Because simple minimisation within centres can, in theory, lead to alternation of treatment allocation, the algorithm also incorporates 30% of random allocation. This helps to ensure concealment.

### Sample size estimation

We hypothesised that the intervention would result in an at least 10% absolute decrease in the primary endpoint, and we assumed that 30% of controls would achieve the primary endpoint. With a 5% two-sided alpha risk and 80% power, 640 patients would be needed [320 in each group]. We assumed that 10% of patients would be lost to follow-up before study completion or would not have data on the primary endpoint. Therefore, we plan to include 704 patients in all.

### Statistical analysis

Data will be analysed according to CONSORT guidelines
[30]. The descriptive analysis will compare the two randomised groups in terms of general characteristics, demographics, co-morbidities, risk factors, and baseline HNSCC characteristics. Only descriptive statistics will be used at this stage. Quantitative variables will be described as mean [±1 standard deviation (SD)] or median [25-75th percentiles] according to their distribution and qualitative variables as numbers [%].

A flow diagram will be created according to CONSORT guidelines. The primary endpoint will be analysed using the intent-to-treat approach, with all patients kept in the group to which they were assigned by the randomisation system. We will compare the proportions of patients achieving the primary endpoint in the two groups using Pearson’s chi-square test, and we will assess effect size by computing the relative risk with its 95% confidence interval [95% CI] and the absolute difference between groups. This analysis will be adjusted for any baseline patient characteristics that are imbalanced between the two groups. For between-group comparisons of secondary endpoints, we will use the same method as for the primary endpoint.

Variables measured serially during follow-up [functional status, depressive mood, weight, pain, and quality of life] will be analysed using mixed models to take into account the repetition of the measures. Quality-of-life data will be analysed using QLQ-C30 and H&N35
[8,31,32]. Subgroup analyses will be conducted according to age group [<or ≥80 years], tumour site, and tumour stage.

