**Methods/design:**

EGeSOR is an open-label, multicentre, randomised, controlled, parallel-group trial in patients aged 70 years or older and receiving standard care for HNSCC. The intervention includes four components: the CGA conducted by a geriatrician before cancer treatment, participation of the same geriatrician in cancer treatment selection, a standardised geriatric therapeutic intervention designed by the same geriatrician; and geriatric follow-up for 24 months. The primary endpoint, assessed after 6 months, is a composite criterion including death, functional impairment [Activities of Daily Living score decrease ≥2], and weight loss ≥10%. Secondary endpoints include progression-free survival, unscheduled admissions, quality of life, treatment toxicities, costs, and completion of the planned cancer treatment. A centralised online system is used to perform 1:1 randomisation with a minimisation algorithm for centre, age, T and N stages, and tumour site [oral, oropharyngeal, hypopharyngeal, or laryngeal]. The estimated sample size is 704 patients, who are being recruited by 14 centres in 9 French cities.

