## Methods/design

### Study design and setting

We are conducting an open-label, multicentre, parallel-group, randomised, controlled trial in patients aged 70 years or older and receiving standard care for HNSCC. One group receives a CGA-based multi-component intervention and the other does not [Figure 
1]. The primary endpoint is a composite criterion to be assessed after 6 months. Other endpoints such as OS and disease-free survival are assessed after 24 months. The patients are being recruited at 14 ENT/maxillo-facial surgery departments in 13 hospitals located in 9 cities in France [Paris, Créteil, Montfermeil, Villeneuve-Saint-Georges, Lille, Strasbourg, Nancy, Nantes, and Suresnes]. The protocol was approved by the appropriate ethics committee [CPP Ile-de-France I, Paris, France, approval April, the 20 April 2013;13213]. The trial is registered on ClinicalTrials.gov [NCT02025062].

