The EGeSOR trial has several limitations. First, the CGA is time consuming and requires extensive involvement of geriatric teams, which may not be available in some centres. We visited each of the study centres to verify that the number of geriatricians was sufficient, and we considered reinforcing the geriatric team if necessary. Second, the primary endpoint is a composite criterion. However, demonstrating superiority of the study intervention on a single endpoint would have required such a large sample size as to compromise feasibility of the trial. Third, contamination bias may occur between the intervention and control groups, as each ENT physician manages patients in both groups. Conceivably, ENT physicians may apply knowledge acquired by managing intervention patients to their control patients, for instance by asking geriatricians for advice regarding vulnerable controls. Such contamination bias would diminish the size of the effect of the intervention. However, any contamination bias is probably limited, since modifications potentially introduced by ENT physicians in controls would have a very small effect compared to the full four-component intervention. Nevertheless, we are recording the number of times that advice from geriatricians is provided for control patients. Our study had several strengths. To our knowledge, it is the first randomised controlled trial evaluating the efficacy of the CGA in elderly cancer patients. We decreased the risk of selection bias by using randomisation with minimisation, the risk of evaluation bias by selecting objective clinical endpoints and using independent adjudication, and the risk of confusion bias by using randomisation with minimisation and a pre-specified multivariate analysis to correct for any baseline between-group imbalances. Finally, the standardised multidimensional geriatric therapeutic programme was designed in accordance with the most recent clinical recommendations and relied on validated international measurement tools.

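### The primary comparison is adjusted for whichever baseline variables look imbalanced rather than for the five minimisation factors, and the decisive result is not named

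*Protocol article*

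**What the plan says.** **Allocation.** Random assignment (Protocol article): "The randomisation system applies a minimisation programme to balance the two groups regarding centre, age" (cut at 80 years), T stage (cut at T2), N stage (cut at N2) and tumour site (four levels). On the random element, "the algorithm also incorporates 30% of random allocation".

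**Primary analysis.** Statistical analysis: the proportions reaching the composite are compared "in the two groups using Pearson’s chi-square test, and we will assess effect size by computing the relative risk" with its 95% CI and the absolute difference. The next sentence is "This analysis will be adjusted for any baseline patient characteristics that are imbalanced between the two groups". Binary secondary endpoints fall under the same method.

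**Baseline comparison.** Same section: "Only descriptive statistics will be used at this stage". So neither a test nor a threshold defines imbalance.

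**Description elsewhere.** The Discussion lists among the trial's strengths "a pre-specified multivariate analysis to correct for any baseline between-group imbalances".

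Age group, tumour site and tumour stage reappear in Statistical analysis only as subgroup variables. Centre does not reappear there.

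**The concern.** There are three linked problems.

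1. **The covariates depend on the data.** They are settled only once baseline characteristics have been tabulated by arm, with no stated criterion. The intention to adjust is fixed in advance; the model is not.
2. **The rule runs against the design.** Minimisation makes its own five factors the least likely to look imbalanced. A rule that selects on imbalance will tend to leave them out and to admit chance differences in other variables, prognostic or not. Balance on a prognostic factor does not remove the reason to adjust for it, because the unadjusted variance still counts variation that the allocation has largely removed from the comparison.
3. **The decisive result is not stated.** Pearson's statistic takes no covariates, so an adjusted analysis means a second, unnamed model. Nothing says which of the two governs the conclusion.

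At stake are a confirmatory analysis that is not uniquely determined and some precision that the design has already earned.

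**Working it through.** **1. The plan's own figure.** Inputs from Sample size estimation: 30% against 20%, two-sided 5%, 80% power, 640 evaluable, 704 in all.

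Pooled formula: n = [1.960·√(2·0.25·0.75) + 0.842·√(0.30·0.70 + 0.20·0.80)]² / 0.10² = 294 per arm (588 in all). With continuity correction: 313 per arm (626). The stated 640 is 2.2% above 626, so it reproduces. At 320 per arm the uncorrected test has 83.3% power, and 640 × 1.10 = 704. This calculation is for an unadjusted comparison, and adjusting for the five factors would not raise it.

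**2. How often chance alone would set the model.** The documents give neither a threshold nor a count of candidate covariates. Assume that imbalanced means p < 0.05 and that K independent variables truly do not differ. Then P(at least one flagged) = 1 − 0.95^K:

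| K | 5 | 10 | 20 | 30 |
|---|---|---|---|---|
| Probability | 23% | 40% | 64% | 79% |

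**3. Effect on the test.** Minimisation was simulated with 14 centres, the five factors, 30% random allocation and N = 640.

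Assumptions, none of them from the documents:
- Factor prevalences: 35% aged 80 or over, 70% T2 or above, 40% N2 or above; sites and centres of equal size.
- Log-odds effects at scale 1: age 0.6, T 0.8, N 0.7, site −0.5 to 0.6, centre SD 0.5. These are multiplied by the scale shown below.
- Ten further baseline variables, five of them with log-odds b each.

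The five-factor model is a linear risk-difference model with robust standard errors. The imbalance rule selects any of the ten further variables that differ at p < 0.05.

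| Factor scale; b | Type I: Pearson | Type I: five factors | Type I: better of Pearson and imbalance-adjusted | Power: Pearson | Power: five factors |
|---|---|---|---|---|---|
| 0; 0 | 5.2% | 5.3% | 5.4% | 82.4% | 81.8% |
| 0.7; 0.3 | 4.8% | 5.3% | 5.2% | 85.5% | 86.4% |
| 1; 0.3 | 3.7% | 4.8% | 4.2% | 82.0% | 84.5% |
| 1; 0.6 | 4.5% | 5.2% | 5.0% | 84.0% | 86.1% |
| 1.5; 0.3 | 3.6% | 5.5% | 4.0% | 85.1% | 87.9% |

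Monte Carlo standard error: √(0.05·0.95/2500) = 0.4 points for type I error and √(0.85·0.15/1500) = 0.9 points for power. Between 38% and 42% of simulated trials had at least one flagged variable, in line with step 2.

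**4. A second simulation.** This one used 704 × 0.90 ≈ 634 evaluable patients, 3,000 runs, moderate assumed effects, and a standardised difference above 0.1 as the imbalance criterion.

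| | Pearson | Imbalance-adjusted | Five factors | Five factors + baseline ADL and weight |
|---|---|---|---|---|
| Type I error | 4.1% | 4.2% | 5.2% | 4.9% |
| Power | 83.8% | 84.2% | 85.9% | 87.5% |

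The SD of the Pearson z under the null was 0.95. Its intervals are therefore about 1/0.95 − 1 = 5% too wide, and 2·[1 − Φ(1.96/0.95)] = 3.9%, consistent with the 4.1% observed. Taking the better of the Pearson and imbalance-adjusted results gave 5.1% false positives.

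**The case against.** The strongest reply is that the plan's test works. Pearson's chi-square holds its level in every scenario, its power exceeds the planned 80%, and even choosing the better of two results stays near 5%. The efficiency loss depends wholly on assumed prognostic strength and vanishes when the factors do not predict outcome (82.4% against 81.8%). All of this stands, and it limits the severity.

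A second reply is that the model, the imbalance criterion and the hierarchy of results are details that an article leaves to the full protocol or analysis plan. It adds that Pearson's test, being the only one named and the one that matches the sample-size calculation, is implicitly primary. That reading is possible and softens the third problem. It does not answer the first two. The article does not stay silent on covariates; it states a selection rule, and the rule is a poor one whatever threshold is later attached.

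A third reply is that the Discussion claims only a procedure declared in advance, not a covariate list. That is fair: the Discussion is loosely worded rather than in flat contradiction with Statistical analysis.

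Readers might also infer more than the documents support:
- *That leaving out baseline ADL and weight is an error.* Both components are already defined as changes from baseline, and nothing in the documents shows that the baseline values predict those changes. Adding them is an option for precision.
- *That the open-label design makes the choice of result worse.* What matters is whether the analyst has seen outcomes by arm. The article also has ADL and weight adjudicated by an assistant blinded to arm.

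**Conclusion.** The point holds as a weakness in how the primary analysis is fixed. The covariates follow from the observed data, the rule tends to exclude the factors that restricted the allocation, and the decisive result is not stated.

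Its size is modest. To the extent that the minimisation factors are prognostic, the Pearson test is conservative (simulated type I error about 3.6% to 4.8%) and gives up about 1 to 3 points of power. If they are not prognostic, nothing is lost. These figures rest on assumed effects, prevalences and centre sizes.

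A reader might conclude that the Pearson test is invalid, that its standard error is wrong in all circumstances, or that the rule inflates false positives. The evidence does not show this. The standard error is too large only if the factors are prognostic. Picking the better result gave 4.0% to 5.4% false positives across both simulations, and the sample size is unaffected. Each simulation did apply one fixed imbalance criterion, whereas the protocol fixes none. The remaining freedom is a matter of discretion whose size was not measured.

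Severity: should be fixed.

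**What to change.** In Statistical analysis, delete the imbalance rule and name one primary analysis, fixed before any outcome data by arm are seen. This would be a regression of the 6-month composite on arm, adjusted for centre (as a random effect, or with small centres pooled), age group, T stage, N stage and tumour site. Report the relative risk and the risk difference, both with 95% CIs, and state that this result is decisive.

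Keep the Pearson chi-square as a supportive analysis. Apply the same approach to the binary secondary endpoints. Reword the Discussion so that it describes a covariate list fixed in advance rather than a correction for observed imbalances. Baseline ADL and weight may be added to the fixed list for precision.

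The cost is wording. The five factors are recorded at randomisation, baseline ADL and weight are needed for the endpoint in any case, and the sample size does not change. The small downside is a model in place of a 2×2 table, with care needed for small centres.

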#### (a) CGA

The CGA is performed by the intervention geriatrician, after randomisation and before the multidisciplinary meeting during which the cancer-treatment plan is established. The CGA consists in a detailed medical, psychological, and social assessment including a careful medical history and physical examination. In accordance with SIOG recommendations for elderly cancer patients, seven domains are assessed routinely: functional status, mobility and fall risk, nutritional status
[25], cognitive status, mood, co-morbidities and medications, and social environment. These domains are assessed using validated tests, questionnaires, scores, and/or scales [Table 
1]. Pain is also evaluated using a verbal numeric scale. The CGA is performed by a senior geriatrician, in some cases with help from a trained healthcare worker [usually a nurse working in the oncology and/or geriatric department].

**Table 1 T1:** Primary and secondary endpoints in the EGeSOR trial

**Endpoints**	**Time assessed**	**Description**
Primary endpoint	6 months after randomisation	Composite criterion including
		- death,
		- at least 2-point decrease in the Activities of Daily Living (ADL) score versus baseline
		- at least 10% decrease in body weight versus baseline
Secondary endpoints	6, 12, and 24 months after randomisation	- each component of the primary endpoint
		- progression-free survival
		- in-hospital death
		- unplanned admissions
		- post-surgery hospital stay length
		- discharge to home or nursing home
		- final cancer treatment plan (surgery, chemotherapy, targeted therapies, radiotherapy, and/or supportive care, alone or combined)
		- quality of life assessed by EORTC QLQ-C30 and specific module for head and neck cancer H&N35
		- treatment toxicities and/or complications: chemotherapy toxicities according to Classification Common Terminology Criteria for Adverse Events (CTCAE version 4.02)
		- cancer treatment feasibility
		- costs

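### The rule that secondary endpoints use the primary endpoint's two-proportion method does not fit progression-free survival, overall survival or length of stay

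*Protocol article*

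**What the plan says.** For the primary endpoint, the Statistical analysis section of the protocol article fixes the test, "We will compare the proportions of patients achieving the primary endpoint in the two groups using Pearson’s chi-square test", and the effect measures, "we will assess effect size by computing the relative risk with its 95% confidence interval [95% CI] and the absolute difference between groups". It then extends this to the rest: "For between-group comparisons of secondary endpoints, we will use the same method as for the primary endpoint".

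Two exceptions are stated:
- Serially measured variables (function, mood, weight, pain, quality of life) "will be analysed using mixed models to take into account the repetition of the measures".
- The Costs section gives costs a Wilcoxon-Mann-Whitney test, parametric tests and bootstrap intervals.

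Table 1 lists the secondary endpoints, to be assessed "6, 12, and 24 months after randomisation". They include "progression-free survival" and "post-surgery hospital stay length". The Study design and setting section adds: "Other endpoints such as OS and disease-free survival are assessed after 24 months". The article mentions no Kaplan-Meier estimate, log-rank test, Cox model or rule for censored patients.

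**The concern.** This is a stated rule, not a detail left to the analysis plan. An analysis plan that named a log-rank test would contradict the sentence.

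A survival endpoint followed to 24 months has event times and some patients whose follow-up ends early. A comparison of proportions ignores the times and offers no proper place for those patients. Length of stay is a duration, so it has no proportion and no relative risk.

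At stake are OS, which comes first in the stated objective, and hospital stay, which the Discussion names among the expected benefits. The terms also disagree. The design section speaks of disease-free survival, while the abstract and Table 1 speak of progression-free survival. Disease-free survival has no clear meaning for patients who never become disease-free, and the intervention section allows palliative treatment goals.

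**Working it through.** **1. The plan's own figure.** The sample size is the only computed design figure. For 30% against 20%, two-sided 5% alpha and 80% power, the usual formula gives 294 per arm (588) without continuity correction and 313 per arm (626) with it, close to the stated 640. The 704 is 640 × 1.10. The point does not depend on these figures.

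**2. Which endpoints the rule fits.**
- Fits: in-hospital death, discharge destination, final treatment plan, and unplanned admission if scored yes/no.
- Exempt: serial measures including quality of life; costs.
- Covered but does not fit: progression-free survival, OS (and disease-free survival, if that is meant), and length of stay, for which no cut-point is given.

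**3. Size for a survival endpoint.** From the documents: 704 patients (352 per arm), 24 months from randomisation, and 10% lost or without primary-endpoint data. Assumed: exponential event times, a hazard ratio of 0.75 for power, and loss of 10% in each arm or 5% (intervention) against 15% (control). There were 3,000 simulated trials per row. The chi-square is applied at 24 months with lost patients either dropped or counted as event-free.

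Deaths by 6 months, if the endpoint were OS, follow from S, the control event-free proportion at 24 months, as 1 − S^(6/24).

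| S at 24 months | Implied events by 6 months | Power, equal loss: log-rank / dropped / event-free | False positives, unequal loss: log-rank / dropped / event-free |
|---|---|---|---|
| 60% | 12.0% | 60.5 / 58.8 / 59.5% | 4.3 / 5.7 / 7.3% |
| 50% (median 24 months) | 15.9% | 71.6 / 70.0 / 69.8% | 5.0 / 7.2 / 9.9% |
| 40% | 20.5% | 78.3 / 74.7 / 75.4% | 5.3 / 6.7 / 11.0% |
| 30% | 26.0% | 85.6 / 80.9 / 79.8% | 5.8 / 7.7 / 13.1% |

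With equal loss and no effect, all three methods stayed at about 5-6%. A separate simulation with loss spread uniformly over 24 months gave, for control medians of 24, 18, 12 and 8 months, log-rank power of 71, 79, 87 and 93%. The chi-square with lost patients dropped had 69, 76, 82 and 84%. Under unequal loss, counting lost patients as event-free gave 10-19% false positives over those medians. The 19% belongs to the fastest events.

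**4. Hand check of the bias (S = 50%, no true effect).** Let a = −ln 0.50 = 0.693 be the event hazard over 24 months. The loss hazard is c = −ln 0.85 = 0.163 (control) or −ln 0.95 = 0.051 (intervention). The observed event proportion is a/(a+c) × [1 − e^−(a+c)].
- Control: 0.810 × 0.575 = 0.466. Intervention: 0.931 × 0.525 = 0.489.
- Lost counted as event-free: 0.489 − 0.466 = +0.023, so the intervention looks worse.
- Lost dropped: 0.489/(0.489 + 0.475) − 0.466/(0.466 + 0.425) = 0.507 − 0.523 = −0.016, so the intervention looks better.

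These agree with the simulated +0.023 and −0.016. The two ways of handling lost patients bias the result in opposite directions, and the article does not say which applies.

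**5. Which scenarios suit OS.** The sample size section assumes that 30% of controls die, lose function or lose weight by 6 months. An 8-month median survival would mean 1 − 2^(−6/8) = 40.5% dead by then, more than the whole composite. A 12-month median gives 29.3%, which leaves almost nothing for the other two components. A 24-month median gives 15.9%, which fits comfortably. The large power gap therefore cannot illustrate OS. It could apply only to a short progression-free survival, for which the article gives no figure.

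**The case against.** The strongest reply is that Table 1 fixes assessment at 6, 12 and 24 months on a common clock from randomisation. There is then no staggered administrative censoring, and a comparison of proportions at a fixed time is valid when status is known for nearly everyone. This stands: with 10% equal loss the bias is negligible and the power cost is 0 to 6 points in the table above.

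Three stronger readings are tempting, and the documents do not support them.
- *Every secondary endpoint gets the wrong test.* The two stated exceptions contradict this, and chi-square suits the binary rows of Table 1.
- *Loss will differ by arm because only the intervention arm gets three-monthly geriatric calls.* Those calls are part of the intervention. Nothing says that outcomes are ascertained through them, and the Costs section records resource use by the same methodology in both groups. Unequal loss is possible in an open-label trial, but 15% against 5% is an assumption.
- *OS is missing from Table 1.* The table lists each component of the primary endpoint at all three times, so death is there, though not under the name OS.

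The reply does not rescue length of stay, and it leaves open how lost patients are handled in the survival comparisons.

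**Conclusion.** As written, the same-method sentence is wrong for length of stay, which cannot be analysed that way without a cut-point. For progression-free survival and OS it is inefficient, and it is open to bias if loss differs by arm. Calling it invalid for survival in every case would go too far.

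On the assumptions shown, the power cost is about 2 points at a 24-month control median and reaches about 10 only with fast events. Under the assumed 15% against 5% loss, false positives are roughly 6-8% with lost patients dropped and 7-19% with them counted as event-free, against about 5% for log-rank. In the table's scenarios, all of which keep 6-month mortality below the planned 30% composite, the latter range is 7-13%. The event rates, hazard ratio and arm-specific losses do not come from the documents.

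The mismatch between disease-free and progression-free survival is a real but separate labelling fault. The primary analysis and sample size are untouched, so this should be corrected but is not critical to the trial's main conclusion.

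**What to change.** - Limit the same-method sentence to binary secondary endpoints, such as in-hospital death, discharge destination and unplanned admission yes/no.
- Analyse OS and progression-free survival from randomisation with Kaplan-Meier estimates and a log-rank test or Cox model, censoring patients at last known status.
- Compare post-surgery length of stay with a rank or continuous method, as the Costs section already does for costs.
- Use one term for the disease-control endpoint in the abstract, the design section and Table 1. Progression-free survival can be defined for all randomised patients.
- Name OS in Table 1, where death now appears only as a component of the primary endpoint.

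The cost is wording only. No extra patients or new data are needed, provided that dates of events and of last contact are recorded during the planned 24 months. The change should be made before any between-arm data are seen.
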